## Interventions

### Aerobic exercise intervention

Participants determined to be exercise tolerant will be instructed to complete 4 weeks [24, 25] of aerobic exercise at the prescribed target heart rate (HR) of 50–65% of age-predicted HR [26, 27]. Participants determined to be exercise intolerant via the Buffalo Concussion Bike Test (BCBT) will be instructed to complete 4 weeks of STAE. The STAE prescription target HR will be 80% of the HR achieved at symptom exacerbation on the BCBT at the most recent visit. All participants will be required to complete 20 min of aerobic exercise of choice at home or in a gym at the individually prescribed HR, monitored by wearing a provided HR tracker (Fitbit Inspire 3). Participants performing STAE will be instructed to stop their exercise session if their symptoms increase by two or more points from their pre-exercise symptom level (on a 10-point Visual Analog Scale) or at 20 min, whichever comes first. All participants will be encouraged to perform 5 min of chosen warm-up and cool down. They will be told to rest apart from the prescribed exercise and not participate in other physically engaging activities. A 4-week intervention was chosen to align with the interventions’ previous interventions using aerobic exercise as a therapeutic intervention for brain injury [24, 25].$$Max\;Heart\;Rate\;=\;210\;-\;0.79\lbrack Current\;Age\rbrack$$$$\begin{array}{c}Goal\;heart\;rate\;=\;(Max\;Heart\;Rate\;-\;Resting\;Heart\;Rate)\;x\;Goal\;Percent\;Effort\;+\\Resting\;Heart\;Rate.\end{array}$$$$\begin{array}{c}\mathrm{Example}:\;45-\mathrm{year}-\mathrm{old}\;\mathrm{woman},\;\mathrm{resting}\;\mathrm{heart}\;\mathrm{rate}\;50\mathrm{bpm},\;\mathrm{goal}\;\mathrm{percent}\;\mathrm{effort}\;60\%\\210\;-\;0.79(45)\;=\;174\\(174-50)\;x\;0.60+50=124+/-10\mathrm{bpm}\end{array}$$

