### Compliance to the intervention

Participants will be withdrawn from the study if there is a change in medications or if they are unable to attend follow-ups. Self-reported compliance to the intervention will be tracked at weekly follow-up visits via REDCap survey. Fitbit data can also verify adherence to exercise protocol and will be quantified via the following formula [61]:$$\mathrm{A}\mathrm{d}\mathrm{h}\mathrm{e}\mathrm{r}\mathrm{a}\mathrm{n}\mathrm{c}\mathrm{e}=\frac{{(\mathrm{v}\mathrm{o}\mathrm{l}\mathrm{u}\mathrm{m}\mathrm{e})}_{\mathrm{a}\mathrm{c}\mathrm{t}\mathrm{u}\mathrm{a}\mathrm{l}}}{{(\mathrm{v}\mathrm{o}\mathrm{l}\mathrm{u}\mathrm{m}\mathrm{e})}_{\mathrm{p}\mathrm{r}\mathrm{e}\mathrm{s}\mathrm{c}\mathrm{r}\mathrm{i}\mathrm{b}\mathrm{e}\mathrm{d}}}\times 100$$$$=\frac{{(\mathrm{H}\mathrm{R}\times \mathrm{t}\mathrm{i}\mathrm{m}\mathrm{e}\times \mathrm{f}\mathrm{r}\mathrm{e}\mathrm{q}\mathrm{u}\mathrm{e}\mathrm{n}\mathrm{c}\mathrm{y})}_{\mathrm{a}\mathrm{c}\mathrm{t}\mathrm{u}\mathrm{a}\mathrm{l}}}{{(\mathrm{T}\mathrm{a}\mathrm{r}\mathrm{g}\mathrm{e}\mathrm{t}\mathrm{H}\mathrm{R}\times 20\times 1)}_{\mathrm{p}\mathrm{r}\mathrm{e}\mathrm{s}\mathrm{c}\mathrm{r}\mathrm{i}\mathrm{b}\mathrm{e}\mathrm{d}}}\times 100$$

The numerator represents the volume of exercise performed divided by the volume of exercise prescribed to the participant. Volume actual is determined by multiplying weekly mean HR recorded during home exercise by weekly mean exercise time in minutes by the number of days per week out of 6 completed (i.e. 3 out of 6 days completed = 3/6 = 0.5). Volume prescribed was determined by multiplying weekly target HR by 20 min by days prescribed (every day excluding scheduled visit = 6/6 = 1). Participants who had an adherence rate of 66.67% or more were adherent, whereas participants with a rate lower than 66.67% were considered to be nonadherent [61].

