### Attrition and adherence

To ensure attrition and program adherence, participants’ HR will be collected using a Fitbit Versa 3 and monitored using Fitabase (Small Steps Labs, LLC) [62], a software that synchronises and displays Fitbit data in real-time. If it is observed that a participant’s HR does not reach within the prescribed range, a member of the research team will check in via text or email. Participants will also be required to complete a written diary given at each follow-up to document the type of exercise they completed, how long they exercised for, and if any PPCS symptoms were triggered by engaging in exercise. Additionally, participants will be offered a $50 e-gift voucher at baseline and at each follow-up to encourage attendance. Participants will be withdrawn if they are unable to complete daily exercise or attend follow-ups.

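### In the aerobic arm, women on sub-symptom threshold exercise (STAE) who follow the stop rule lose adherence credit, and can be classed nonadherent, because prescribed time is fixed at 20 min

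*Protocol article*

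**What the plan says.** Section *Compliance to the intervention* of the protocol article defines adherence as actual volume divided by prescribed volume, times 100. For the numerator, "Volume actual is determined by multiplying weekly mean HR recorded during home exercise by weekly mean exercise time in minutes", and then by the share of the 6 weekly home days completed, with the worked term "3 out of 6 days completed = 3/6 = 0.5". For the denominator, "Volume prescribed was determined by multiplying weekly target HR by 20 min by days prescribed", where the days term equals 6/6 = 1. Target heart rate is individual; the 20 min is a constant with no exception for STAE. The classification follows: "Participants who had an adherence rate of 66.67% or more were adherent", and anyone lower is nonadherent.

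Section *Aerobic exercise intervention* describes session length in two ways. In general, "All participants will be required to complete 20 min of aerobic exercise of choice". Women found exercise-intolerant on the bike test, who receive STAE, are "instructed to stop their exercise session if their symptoms increase by two or more points from their pre-exercise symptom level", or at 20 min if that is reached sooner.

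Section *Attrition and adherence* adds a written diary of exercise type, duration and "if any PPCS symptoms were triggered by engaging in exercise". The adherence formula makes no use of the symptom entry.

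**The concern.** The denominator is meant to be what the participant was prescribed. For a woman on STAE the printed instruction is conditional: exercise until the symptom criterion or 20 min, whichever is earlier. A session that ends at 10 min because the criterion was met follows that instruction completely, but the formula credits it with half a session. The score then mixes two different events: not following the programme, and following its stop instruction.

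Adherence is a declared outcome of the trial (abstract; Table 1, under compliance and feasibility; section *Data analysis*, as a proportion), and the article says the results will inform self-directed treatment plans. If exercise-intolerant women show lower adherence, a reader could not tell whether they disregarded the programme or complied with it.

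**Working it through.** **Inputs.** From *Compliance to the intervention*: numerator = weekly mean HR × weekly mean minutes × (days completed / 6); denominator = target HR × 20 × 1; cut-off 66.67%. From *Aerobic exercise intervention*: the STAE stop instruction. Not given anywhere: the share of women on STAE, how often they stop early, and at what minute. Stopping times below are therefore illustrations.

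**Formula.** Let h = mean HR / target HR, m = weekly mean minutes, d = days completed. Then

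Adherence = h × (m / 20) × (d / 6) × 100.

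**Reproducing the plan's own terms.** With h = 1 and m = 20, d = 6 gives 100% and d = 3 gives 50%. These match the printed 6/6 = 1 and 3/6 = 0.5.

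**Break-even mean session.** m* = 0.6667 × 20 / (h × d/6).

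| h | d | m* (min) |
|---|---|---|
| 1.0 | 6 | 13.33 |
| 1.0 | 5 | 16.0 |
| 0.9 | 6 | 14.82 |
| 1.1 | 6 | 12.12 |

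**A woman who follows the stop rule on all 6 days at target HR** scores 5 × m per cent:

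| Mean session (min) | Score | Class |
|---|---|---|
| 8 | 40% | nonadherent |
| 10 | 50% | nonadherent |
| 12 | 60% | nonadherent |
| 13 | 65% | nonadherent |
| 14 | 70% | adherent |
| 15 | 75% | adherent |
| 18 | 90% | adherent |

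**Occasional stops.** With k stopped sessions of t minutes and 6 − k full ones, m = (k·t + (6 − k)·20)/6.
- t = 10, k = 3: m = 15, score 75%.
- t = 10, k = 5: m = 11.67, score 58.3%.
- t = 5, k = 2: m = 15, score 75%.
- t = 5, k = 3: m = 12.5, score 62.5%.

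**Does a stopped session count as a completed day?** The section does not say. Take two stops at 10 min and four full sessions: m = (20 + 80)/6 = 16.67. If all six days count, the score is 16.67/20 × 6/6 = 83.3%. If the two stopped days lose their day credit but stay in the mean, it is 16.67/20 × 4/6 = 55.6%. The tables above take the more favourable reading.

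**With prescribed minutes set to the minutes at which the rule was met**, a woman who complies on all 6 days at target HR scores m/m = 100% whatever her stopping time, against 40% at 8 min, 60% at 12 min or 75% at 15 min under the printed formula.

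**The case against.** The strongest defence is that the 20-min denominator has a basis in the text: the intervention section does require 20 min of all aerobic participants. Delivered volume over a full 20-min volume is a coherent measure of dose received. That stands, and it is a reason to keep the figure under that name. It does not make the figure a measure of following instructions when the same section gives STAE women a conditional stopping time.

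Second, early stops may be uncommon. The STAE target is 80% of the heart rate at symptom exacerbation on the most recent bike test, and the test is repeated weekly, so the prescription is intended to stay below the symptom threshold. The one-third margin below 100% also absorbs occasional stops: three at 10 min still give 75%. This stands too, and it is why the size of the bias is unknown.

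Third, this formula is not the only record; self-reported compliance is collected weekly and a diary is kept. True, but the adherent/nonadherent classification is attached to the formula.

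A reader might infer that every woman who obeys the stop rule is scored nonadherent. The arithmetic does not support that: she loses credit, but crosses the cut-off only below the break-even mean. A reader might also infer that the whole trial is affected. The formula needs a target heart rate, and none is stated for the stretching arm, so only the STAE part of the aerobic arm is concerned.

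**Conclusion.** The point holds in limited form. The intervention and compliance sections contradict each other on what an STAE participant is prescribed. As printed, the formula takes credit from sessions ended as instructed unless heart rate above target offsets the loss. Full compliance can be classed as nonadherence: below a weekly mean of about 13.3 min on 6 of 6 days, or 16 min on 5 of 6, both at target heart rate and with stopped sessions counted as completed days.

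Wherever such stops occur, the adherence proportion is pulled downward for exercise-intolerant women. The documents give no figure from which to estimate by how much. If no one stops early, the bias is nil.

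It is tempting to carry this through to the primary result, because women who do not complete the 4 weeks are left out of the primary endpoint analysis and those unable to complete daily exercise are withdrawn. Neither rule refers to the 66.67% cut-off; the exclusion is explained as loss to follow-up. No outcome comparison by adherence is announced either. The consequence shown is confined to a secondary, descriptive outcome.

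**What to change.** 1. Reconcile *Aerobic exercise intervention* with *Compliance to the intervention* on what an STAE session is prescribed to be. Which clinical rule stands is for the sponsor.
2. If the stop instruction stands as printed, compute adherence-as-prescribed at session level: the sum over the 6 days of (HR × minutes) divided by the sum of (target HR × prescribed minutes). Prescribed minutes equal the minutes reached for a session ended by the stop rule, and 20 for every other day, including missed days. Count a stop-rule day as completed. Missed days still cost credit. For example, with four stops at 10 min, one full session and one missed day, all at target heart rate, the score is 60/(40 + 20 + 20) = 75%. The printed formula gives (12/20) × (5/6) = 50%.
3. Report the present volume against 20 min beside it, labelled as dose received.
4. Add one diary item: was this session ended by the stop rule? The diary as described records duration and triggered symptoms, but not whether the rise reached two points.

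**Cost.** One diary item, one derived variable, and a move from weekly means to sessions. The downside is that stop-rule sessions rest on self-report and receive full time credit by construction. The trial was recruiting at submission, with data collection expected to end on 16/05/2027, so women who finish before the item is added will lack it. For them, the figure can be bounded by counting either all or none of their short sessions with triggered symptoms as stop-rule sessions.

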### Placebo stretching intervention

Participants assigned to the control passive stretching group will be instructed to follow a prescribed stretching program. This group will be provided with a booklet containing a gentle, whole-body, progressive stretching program (with pictures and instructions) that does not considerably elevate HR to perform for 20 min per day for 4 weeks. Participants will be asked to return weekly to re-evaluate performance on the BCBT. All participants will be encouraged to perform 5 min of chosen warm-up and cool down. They will be told to rest apart from the prescribed exercise and not participate in other physically engaging activities. Following 4 weeks of passive stretching intervention, participants will be re-evaluated for exercise intolerance and offered the option to participate in the 4-week aerobic exercise intervention.

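### The adherence score does not match the exercise prescription: it passes sessions well below the target intensity and can fail STAE participants whose sessions end early as instructed

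*Protocol article*

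**What the plan says.** Compliance to the intervention forms the actual volume thus: "multiplying weekly mean HR recorded during home exercise by weekly mean exercise time in minutes by the number of days per week out of 6", counting the days on which a session was done. The prescribed volume comes from "multiplying weekly target HR by 20 min by days prescribed", with the days term equal to 6/6 = 1. The ratio is expressed as a percentage and dichotomised: "Participants who had an adherence rate of 66.67% or more were adherent". The formula and the cut are both attributed to a cited study.

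Aerobic exercise intervention sets what is being adhered to. Exercise-tolerant women train "at the prescribed target heart rate (HR) of 50–65% of age-predicted HR", but the equation and worked example that follow use heart-rate reserve: resting rate plus a percentage of the distance from resting to maximum. For exercise-intolerant women, "The STAE prescription target HR will be 80% of the HR achieved at symptom exacerbation on the BCBT at the most recent visit". A session is 20 min, with one exception: "Participants performing STAE will be instructed to stop their exercise session if their symptoms increase by two or more points".

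The stretching programme in Placebo stretching intervention is one "that does not considerably elevate HR to perform for 20 min per day for 4 weeks". It has no target heart rate.

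Table 1 lists compliance and feasibility as a secondary outcome, and Data analysis reports adherence as a proportion.

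**The concern.** Score and prescription are built differently in three respects.

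- The score credits the resting heart rate and does not cap minutes, so low intensity is only lightly penalised and extra minutes can make up for it.
- It holds everyone to 20 min, including women told to stop sooner when symptoms rise.
- It needs a target heart rate, which only one arm has.

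At stake is a named secondary outcome that readers will use to judge whether the intervention was delivered as planned. The errors run in both directions and do not fall evenly: the false nonadherent label can fall only on symptomatic, exercise-intolerant women.

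**Working it through.** **Inputs from the protocol.** Maximum heart rate 210 − 0.79 × age; worked example of age 45, resting 50, 60% effort, target 124 ± 10 bpm; cut 66.67%; 20 min; six days per week. **Assumptions, because the protocol gives no figures:** resting rates of 70 and 80 bpm, and an STAE symptom threshold of 120 bpm.

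**1. Reproduce the plan's figure.** 210 − 0.79 × 45 = 174.45 (stated as 174). (174 − 50) × 0.60 + 50 = 124.4 (stated as 124). It reproduces.

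**2. Heart rate that just passes, 20 min on 6/6 days.** Minutes and days cancel, so passing rate = 0.6667 × target. Share of reserve = (passing rate − resting) / (maximum − resting).

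| Resting rate | Target (60%) | Passing rate | Above rest | Share of reserve |
|---|---|---|---|---|
| 50 (protocol example) | 124.7 | 83.1 | 33.1 | 26.6% |
| 70 (assumed) | 132.7 | 88.5 | 18.5 | 17.7% |
| 80 (assumed) | 136.7 | 91.1 | 11.1 | 11.8% |

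The table uses the unrounded maximum of 174.45. With the rounded target of 124, the first row gives 82.7 bpm and 26.3%. The lower edge of the example's own tolerance, 114 bpm, would score 114/124 = 92%, so the cut lies about 30 bpm below that edge.

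**3. Other targets.** If the target is read literally as 50–65% of age-predicted heart rate, it is 0.50 × 174 = 87 to 0.65 × 174 = 113 bpm, and the passing rate is 58 to 75 bpm. For STAE with an assumed threshold of 120 bpm, the target is 0.80 × 120 = 96 and the passing rate is 64 bpm.

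**4. Uncapped minutes.** In the worked example, a recorded mean of 30 min would pass at 82.7 × 20/30 = 55 bpm.

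**5. Symptom stop at exactly the target rate.** The score reduces to (mean minutes / 20) × (days / 6).

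- Needed to pass: 0.6667 × 20 = 13.3 min on 6/6 days, or 13.33 / (5/6) = 16.0 min on 5/6 days.
- Stopping at 10 min in every session: 50%, nonadherent.
- Stopping at 13 min in every session: 65%, nonadherent.
- Stopping at 14 min in every session: 70%, adherent.
- Stopping at 10 min in three of six sessions: mean 15 min, 75%, adherent.

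**6. Effect of scoring heart rate above rest (worked example, target 124).** The passing rate moves from 82.7 to 50 + 0.6667 × 74 = 99.3 bpm, and a session at 83 bpm scores 33/74 = 45% instead of 67%.

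**The case against.** The strongest reply is that the formula comes from a cited study, that it serves a descriptive outcome, and that other safeguards exist. Attrition and adherence describes real-time heart-rate monitoring with a check-in when the prescribed range is not reached, and a diary of exercise type, duration and triggered symptoms. Compliance is also surveyed weekly without restriction by arm. The STAE target lies below the symptom threshold and can be reset at each weekly test, so early stops at every session are not a given. All of this stands, but none of it enters the score or says how a rule-stopped session is counted.

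Five stronger readings are tempting and are not supported.

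- *Near-resting activity passes in general.* In the worked example the passing rate is 33 bpm above rest. Coming close to rest needs a higher assumed resting rate, a low STAE target, the lower end of the literal target, or extra recorded minutes.
- *Doing nothing earns 40–60%.* That is the ratio of resting to target heart rate. With no exercise, minutes and days are zero and the score is 0%.
- *STAE participants who obey the stop rule fail.* Only those with a short enough weekly mean do.
- *Adherence cannot be compared between arms.* Only this formula cannot; the weekly survey covers both arms, although the article states no common quantitative measure.
- *The primary result is affected.* Data analysis excludes women who do not complete the four weeks, described as loss to follow-up. Neither that exclusion nor the withdrawal rules refer to the 66.67% class.

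**Conclusion.** The concern holds in limited form. The score and the prescription disagree, and the disagreement misclassifies participants in both directions. On the protocol's own figures, about 83 bpm passes against a target of 124, or 26–27% of reserve where 60% was prescribed. With assumed resting rates of 70–80 the share falls to about 18–12%. An STAE participant at target rate is classed nonadherent when her mean session is under 13.3 min on 6/6 days, or under 16 min on 5/6, even if each stop was as instructed.

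The reserve figures rest on the equation and worked example. The sentence introducing the target describes it as a percentage of age-predicted heart rate, and the two statements must be reconciled; on the literal reading the passing rate is lower still. How many women would be misclassified cannot be worked out from the document. The point is worth correcting, but it concerns the adherence outcome and its interpretation, not the primary analysis.

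**What to change.** Reconcile Aerobic exercise intervention with Compliance to the intervention on the definition of the target and on how a session stopped under the symptom rule is scored. Then:

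- Score a session stopped under that rule as completed, and record the reason for stopping in the diary or weekly survey.
- Score intensity on the scale of the prescription: heart rate above rest, or minutes within the prescribed heart-rate tolerance from the Fitabase record. Cap minutes at those prescribed per session. For STAE, where a single target and no tolerance is stated, the scoring definition must be written down. If a yes/no class is wanted on the new score, name its cut-off before the data are examined.
- Report sessions completed out of 24 (four six-day periods in Table 2) in both arms as the common measure.
- Keep the cited formula and the 66.67% cut as a secondary descriptive figure.

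The cost is small: analysis wording plus one item in the diary or survey. Heart rate, diary and survey data are already collected. Women who have already finished will lack the reason for stopping, and their diary entry on triggered symptoms is the nearest substitute. The adherence figure may be less favourable and less directly comparable with the cited study. No change to the exercise prescription or the stop rule is proposed.

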### Attrition and adherence

To ensure attrition and program adherence, participants’ HR will be collected using a Fitbit Versa 3 and monitored using Fitabase (Small Steps Labs, LLC) [62], a software that synchronises and displays Fitbit data in real-time. If it is observed that a participant’s HR does not reach within the prescribed range, a member of the research team will check in via text or email. Participants will also be required to complete a written diary given at each follow-up to document the type of exercise they completed, how long they exercised for, and if any PPCS symptoms were triggered by engaging in exercise. Additionally, participants will be offered a $50 e-gift voucher at baseline and at each follow-up to encourage attendance. Participants will be withdrawn if they are unable to complete daily exercise or attend follow-ups.

### Data management and storage

All data will also be coded in a re-identifiable manner and securely stored via REDCap on the Monash University server. A master code linking re-identifiable details will be kept in a secure password-protected database REDCap. The manager of the linking data is PI [name]. Only researchers who are actively contributing to data collection, statistical analysis, and publication will have access to the data. Any hardcopy data will be stored in a locked drawer in the Alfred Centre, accessible only by the investigators. All fluid-based samples will be coded (i.e. re-identifiable) and stored in an ultralow temperature (−80 °C) freezer housed in labs within the Department of Neuroscience, Monash University, until they are analysed. The freezer will only be accessed by the investigators of this study. During the study, participants will be required to wear a Fitbit (Inspire 3) activity tracker. The device must be paired to their mobile phone and synced to the research platform Fitabase. Only data related to HR, steps taken, activity intensity, calories burned, and sleep rating will be collected. No other data from their mobile phone or daily life will be exported to the institute. It is important to note that the collected data will be used solely for the purposes of the study and will be kept confidential. Given that this study involves self-directed aerobic exercise among participants screened via the PAR-Q and assessed for cardiovascular risk, a data safety monitoring board was not considered necessary. Further, as this trial will be conducted at a single site, oversight of the trial will be managed by the research team. As such, a steering committee and data quality committee were not deemed necessary.

Any amendments to the study protocol will be sent to the Monash Human Research Ethics Committee and will not be implemented until approval. Amendments will also be sent to the PI to be added to the Investigator Site File. Any deviations from the approved protocol will be documented using a breach report form.

